**Figure 1 F1:**
[figure not shown]
NUHS@home patient journey.

**Table 1 T1:** The scale-up framework as applied to NUHS@home.

Phases	Set-up	Develop the scalable unit	Test of scale-up	Go to full-scale
Timeline	2020–2022	2022–2024	2024–2025	2025–2030
Bed capacity	3 beds	25 beds	50–100 beds	300 beds

### Study design

This is a retrospective observational cohort study to evaluate implementation outcomes using the EPIS framework during the planned scale-up of NUHS@Home over 23 months. The primary methodology will be quantitative in approach, supported by an explanatory qualitative study with the implementation team to understand which factors are associated with the assessed implementation outcomes and how. The period of data collection will begin with the transition to phase 2 (‘develop the scalable unit’), between May 2022 to April 2024.

### Sample selection

This study will evaluate NUHS@Home, the HaH service at NUHS. NUHS@Home functions as an inpatient substitute service, replicating elements of ward-based care in the home environment. Referrals are accepted from all partner institutions in the health system, including wards, emergency departments, and primary and community care facilities. Patients are assessed for suitability based on the following criteria: (1) clinical stability, (2) ability to receive the required clinical interventions at home, (3) ability to manage toileting independently or with an available caregiver, and (4) living within the geographical catchment (Western Singapore).

The service delivery process can be summarized in four steps (Figure 1)—patient identification, set-up, daily review at home, and discharge.

Key members of the implementation team include leads from physicians, nurses, pharmacy, allied health, and operations. During the initial pilot phase, the implementation team identified 4 key priorities for scale-up: (1) development of new clinical pathways to generate demand for virtual beds, (2) recruitment and training of staff to provide inpatient-level care at home, (3) optimization of internal workflows and processes to ensure both patient safety and provider efficiency, and (4) advocacy for sustainable healthcare financing and billing. The relevant activities and EPIS contextual factors are detailed in Table 2.

**Table 2 T2:** Priorities and activities for scale-up.

Priorities for scale up	Activities	Relevant contextual factors (EPIS)
Overall	Building an implementation team to plan and execute the following activities	Organizational characteristics (IC) Leadership (IC)
Development of new clinical pathways to generate demand for virtual beds	Working with multiple clinical stakeholders to expand clinical pathways.	Institutional leadership (OC) Patient/client characteristics (OC) Patient/client advocacy (OC)
Recruitment and training of staff to be able to provide inpatient level care in the home	Development of accreditation frameworks, careers tracks and training programs for new clinical staff	Organizational staffing (IC) Individual characteristics (IC)
Optimizing internal workflows and processes to achieve both patient safety and provider efficiency	Engaging clinical governance, medicolegal and medical informatics to develop efficient and effective work processes	Quality and fidelity of monitoring/support (IC) Infrastructure (IC) Patient/client advocacy (IC)
Advocating for sustainable healthcare financing and billing	Advocacy for healthcare policy shifts	Funding (OC) External networks (OC)

OC, outer context; IC, inner context.

### Measurements and outcomes

The primary implementation outcomes—defined as ‘the effects of deliberate and purposive actions to implement new treatments […] and are distinct from service and client (patient) outcomes’ (22)—of the scale-up process are as follows:
1.Volume: number of patient admissions to NUHS@Home and associated bed days per month2.Operational efficiency: bed occupancy rate of NUHS@Home, defined as the number of bed days occupied/virtual bed capacity * number of days that month3.Adoption: proportion of patients admitted to NUHS@Home/total patients admitted to affiliated hospital wards for established clinical pathways. Within the NUHS setting, these currently include: cellulitis, urinary tract infections, gastroenteritis, dengue fever, and exertional rhabdomyolysis, but may increase with the development of new clinical pathways.Relevant clinical outcomes will include the rate of unplanned returns to hospital, 30-day readmission rate, HaH mortality rate, and rate of patient safety incidents. At the initial set-up of the NUHS@Home service, our team developed a list of patient safety indicators by reviewing inpatient hospital reporting guidelines and adapting them for NUHS@Home. These indicators include: (1) diagnosis, treatment and procedure-related complications, (2) laboratory medicine and sample-related complications, (3) peripheral venous complication-related complications, (4) medication-related complications, (5) patient falls, (6) pressure injuries, (7) sharps injury and body fluid splash related and (8) staff and visitor incidents. These indicators will be tracked throughout the study period.

In addition, basic patient demographic data (e.g., age, gender) will also be collected to provide descriptive context for the implementation analysis.

A key tenet of implementation theory is that the scale-up process and the associated outcomes of that process (summarized above) will potentially be impacted by, or at least associated with, the context of the implementation. To better understand the impact of context, we applied the EPIS framework to define contextual influences on the outcomes described above and developed a corresponding measurement plan, summarized in Table 3.

**Table 3 T3:** Measurements of contextual influences.

Measurement (per month)	Definition
Implementation outcomes (IO)	
Volume	• Number of patient episodes • Number of bed days
Operational efficiency	• Bed days occupied • Virtual bed capacity
Adoption	• Patients admitted to NUHS@Home per clinical pathway • Total patients admitted to affiliated hospital wards for same clinical pathway
Clinical outcomes (CO)	
Clinical outcomes	• Rate of unplanned return to hospital • 30-day readmission rate • Within HaH mortality rate • Rate of patient safety issues
Outer context (OC)	
Service environment	• Bed occupancy rates of referring hospitals • Lodger volume in emergency department of referring hospitals • Number of active clinical pathways with NUHS@Home
Funding	• Source of service funding used
Institutional leadership	• Number of leadership broadcasts (and content)
External networks	• Number of engagements with external organizations
Patient/client characteristics	• Number of patients referred for each clinical pathway • % patients accepted and rejected for each clinical pathway
Patient/client advocacy	• Number of publicity material to patients and doctors
Inner context (IC)	
Organizational characteristics	• Structural changes in the organization
Leadership	• Components of leadership team
Quality and fidelity of monitoring/support	• Processes for safety review and data tracking • New policies/guidelines/clinical standard/quality indicators • Technology systems used • Volume of home visits, during and after office hours
Organizational staffing processes	• Volume of staff on service, in total, who left • Training programs for staff in existence • Referral hours (office hours, after hours, weekends)
Individual characteristics	• % staff that are permanent or rotated • Demographics, training, experience of each staff
Infrastructure	• Structure of clinical command center, pharmacy, diagnostic, lab • # of vendors, types, issues/challenges, volume of services
Patient/Client Advocacy	• Average patient satisfaction scores • % of patients who returned to hospital due to changing their mind

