### Data collection and data sources

Data sources for this study will include chart review from electronic medical records, human resources data, operational data, and standardized questionnaires disseminated to the NUHS@Home Implementation Team. Collected data will be consolidated into data collection forms (DCFs) on a monthly basis (i.e., 23 data points in total) by a study team member (SL). The DCFs are available in the Supplementary Material, and the data collection strategy is summarized in Table 4.

**Table 4 T4:** Data collection strategy.

DCF	Data	Participants	Data sources
DCF 1 (operational data)	• Indicators of volume and utilization • Outcome indicators • Patient satisfaction indicators • Average occupancy rates of referring hospitals • Average number of emergency department lodgers in referring hospitals • Volume of patients in each clinical pathway • Number of home visits conducted	Operations team	Chart review Clinical operations databases Patient satisfaction team
DCF 2 (service structure and organization)	• Source of service funding • Operating and shift hours • NUHS@Home Leadership & Administrative team	Program lead	Operations data
DCF 3 (clinical operations)	• Referral parameters for active clinical pathways • New/modifications in Clinical Guidelines	Clinical service lead	Operations data Chart review
DCF 4 (service development activities)	• Publicity Broadcasts (by hospital leadership) • Publicity Broadcasts (to staff) • Publicity Broadcasts (to patients) • Engagements with external organizations • Quality and Safety Review Process • New/modifications in Policies • Technology Systems Used • Infrastructure change(s) • External Service Vendors	Operations team to draft a response but all leads to review	Operations data
DCF 5 (staffing)	• Operating and shift hours • Clinical organizational staffing • Clinical staff • Staff demographics • Staff training	Clinical, nursing, pharmacy, allied health and operations lead to fill in separately	Operations data Human resources data

DCF, data collection form.

Color coding: implementation outcome, clinical outcome, outer context, inner context.

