### Data analysis

Both implementation and clinical outcomes will be described descriptively over time to contextualize the scale-up process. We will also use statistical process control (SPC) graphs to examine variation in the three defined implementation outcomes over time. To determine the association of different contextual factors with these outcomes, each contextual factor will first be categorized as either continuous (e.g., bed occupancy rates of referring hospitals) or binary/descriptive (e.g., change in funding source). For continuous variables, unadjusted and adjusted linear regression will be used to statistically assess associations between the number of contextual factors and their values and each implementation outcome to determine whether certain contextual factors are more influential than others. For binary/descriptive variables, contextual events will be annotated on the SPC graphs to assess if a clinically significant relationship exists. These analyses will be supplemented with multivariable regression to adjust for potential confounders. This approach has been previously applied in a similar ‘naturalistic’ implementation evaluation of a hospital-based scaled intervention in the UK (25).

Qualitative data from focus group discussions and meeting minutes will be analyzed using Atlas.ti software, guided by Braun and Clarke's thematic analysis approach (26). Chat logs, transcripts, and observations will be coded inductively, i.e., without any theoretical preconceptions, and themes reflecting implementation aspects will be identified and summarized. In the first stage, data will be deconstructed systematically into first-order concepts. In the second construction stage, the concepts previously developed will be reassembled into new patterns and a constant comparison technique will be carried out to compare the incidents applicable to each emerging theme. The third and final stage of analysis will include the confirmation of the conceptualization of the new phenomenon and a descriptive narrative summary will be created using second-order concepts. The analysis will seek to establish whether the emerging theme represents a barrier or a driver. Results from the different methods will be triangulated for the final data analysis.

Interim analyses will be conducted every three months, with feedback provided to the implementation team as needed.

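### Volume is defined as a raw monthly total with no allowance for month length, unlike the neighbouring occupancy outcome; the effect is small and falls mainly on bed days near capacity

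*Protocol article*

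**What the plan says.** All references are to the Protocol article.

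- **Volume.** Measurements and outcomes lists the first primary implementation outcome as "number of patient admissions to NUHS@Home and associated bed days per" month. Table 3, whose measurements are monthly, gives it as plain counts: "Number of patient episodes • Number of bed days".
- **Occupancy.** The second outcome in the same list is defined as "the number of bed days occupied/virtual bed capacity * number of days that month". Days in the month appear here, but no brackets are printed.
- **Unit of analysis.** Data collection and data sources makes the calendar month the data point: "on a monthly basis (i.e., 23 data points in total"). Study design places data collection "between May 2022 to April 2024".
- **Use.** Data analysis plans "statistical process control (SPC) graphs to examine variation in the three defined implementation outcomes over time", so volume is charted. Each implementation outcome is also regressed on the continuous contextual factors by linear regression, and binary or descriptive events are marked on the charts. No per-day rate, offset or day-count covariate is given for volume. The confounders for the multivariable models are not listed.

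**The concern.** A monthly total rises and falls with the number of days in the month even when the service does not change. The occupancy outcome shows that the authors saw this for one measure, but volume, next to it in the list, does not get the same treatment.

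Two things could follow. On a control chart, February totals sit low and the following March steps up, for calendar reasons only. Contextual events are judged by eye against those same charts, so a calendar step can sit beside an annotation. In the regressions, month length adds to the residual variance. Because some contextual factors in Table 3 are also monthly counts (home visits, for example), it can enter both sides of a model that has only about 23 points.

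**Working it through.** The article states no figure for calendar variation, so there is none to reproduce. The inputs are the stated window, the 1,012 expected admissions over 23 months (Sample size), the pilot's 108 episodes in one year on 3 beds (The intervention), and the 3 and 25 beds of Table 1.

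**1. Month lengths.** May 2022 to April 2024, counted inclusively, is 24 calendar months: 14 of 31 days, 8 of 30, one of 29 and one of 28.
- Total: 434 + 240 + 29 + 28 = 731 days; mean 731/24 = 30.46.
- The squared deviations sum to 13.96. The SD is √(13.96/24) = 0.763, or 0.779 with divisor 23, so the CV is 2.5% to 2.6%.
- The article says 23 months. Dropping either end month leaves the range at 28 to 31 days and the CV at about 2.6%.

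**2. Month-to-month change from length alone.**

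| Step | Change |
|---|---|
| Jan to Feb 2023 | 28/31 - 1 = -9.7% |
| Feb to Mar 2023 | 31/28 - 1 = +10.7% |
| Jan to Feb 2024 | 29/31 - 1 = -6.5% |
| Feb to Mar 2024 | 31/29 - 1 = +6.9% |
| All other steps | 0 to 3.3% in size |

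**3. Admissions.** The planned average is 1,012/23 = 44 per month.
- Poisson SD √44 = 6.6, a CV of 15.1%, against about 2.5% for month length.
- Variance from month length: (44/30.46)² × 13.96/23 = 1.27. Share of variance around a flat mean: 1.27/(1.27 + 44) = 2.8%.
- A 3-sigma count chart centred on 44 has limits 44 ± 3√44, or 24.1 to 63.9. The exact Poisson chance of a point outside them averages 0.39% over the actual month lengths, against 0.35% with month length removed.

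**4. Against planned growth.** Assumption: admissions grow linearly with beds from 3 to 25 at the pilot rate of 108/12/3 = 3 per bed-month, that is from 9 to 75 per month. Expected raw totals then have an R² of 0.997 with the true growth line.

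**5. Bed days.** Assumption: a steady service with 25 full beds. A 28-day month gives 25 × 28 = 700 bed days and a 31-day month gives 25 × 31 = 775. Average daily census is 25 in both.

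**6. Occupancy.** Take 80% use of 25 beds: 560 bed days in 28 days, 620 in 31.
- Intended reading: 560/(25 × 28) = 0.80 and 620/(25 × 31) = 0.80. Month length cancels.
- Read left to right as printed: 560/25 × 28 = 627 and 620/25 × 31 = 769. The swing becomes (31/28)² - 1 = 22.6%.

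**The case against.** **It is an ordinary definition, and the rest may be settled elsewhere.** Monthly admissions and bed days are a normal way to report scale. The article does not fix the chart type, the scaling or the covariates, and a fuller protocol or analysis plan may set a per-day rate. This stands in part: nothing in the article excludes an adjustment. But the outcome is defined as a total, the analysis names that outcome, and an unlisted set of confounders does not supply a day term.

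**Occupancy already offers a day-standardised view.** A reader who sees bed days dip while occupancy stays flat can recognise the artefact. This helps only on the intended bracketing. Occupancy also moves with capacity, so it does not replace a measure of volume in a service that is adding beds.

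**The effect is small.** This stands. The swing near 10% belongs to one February, and for admissions the calendar is minor beside count noise and planned growth.

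Two stronger readings are tempting. A reader might infer that month length makes up a large share, even half, of bed-day variance. Half would require the monthly census to vary by no more than month length does, a CV of about 2.5%, or 0.5 bed at a census of 20. The article gives no census SD, and it describes a service planned to grow from 3 to 25 beds. A reader might also infer that a February dip will be wrongly credited to an annotated event. The article names no such event, and growth could mask the dip.

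**Conclusion.** The point holds as a minor, free improvement. Volume as defined carries month-length variation that the charts and regressions described in the article do not remove. For admissions the gain is slight: about 3% of variance at 44 per month, assuming Poisson counts around a flat mean. It is worth having mainly for bed days when the service runs steadily near capacity, where 700 and 775 can describe an unchanged service. The 25-bed illustration assumes full and constant occupancy. No conclusion of the study is shown to be at risk.

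The missing brackets belong to the same point. The evident intent of the occupancy formula is sound, but read literally it enlarges the calendar effect that it should cancel.

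**What to change.** - Chart and model volume as admissions per day (admissions / days in month) and average daily census (bed days / days in month). Alternatively, fit a count model with log(days) as an offset; the offset belongs in a log-link model, so if linear regression is kept, use the per-day rates.
- Keep the raw monthly totals in a descriptive table, where they show the scale reached.
- Print occupancy as bed days / (virtual bed capacity × days in month).

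The cost is one division of data already collected and one pair of brackets. No new data are needed.

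### Adoption is called a proportion, but its denominator as worded leaves out patients admitted directly home, and whether it is pooled or per pathway is not fixed

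*Protocol article*

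**What the plan says.** The protocol article, under *Measurements and outcomes*, defines adoption as the "proportion of patients admitted to NUHS@Home/total patients admitted to affiliated hospital wards for established clinical pathways". It names five current pathways and adds that these are not final, "but may increase with the development of new clinical pathways".

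Table 3 lists two monthly components for adoption: "Patients admitted to NUHS@Home per clinical pathway" and "Total patients admitted to affiliated hospital wards for same clinical pathway". The denominator is again ward admissions, but the counting is by pathway.

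Under *Sample selection* the service is described as a substitute for inpatient care, and "Referrals are accepted from all partner institutions in the health system, including wards, emergency departments, and primary and community care facilities". The first of the four scale-up priorities is "development of new clinical pathways to generate demand for virtual beds". Table 3 also lists "Number of active clinical pathways with NUHS@Home" as an outer-context measure.

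Under *Data analysis*, the three implementation outcomes go onto statistical process control charts. Linear regression is used to relate each outcome to the continuous contextual factors.

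Operational efficiency is a bed occupancy rate, "defined as the number of bed days occupied/virtual bed capacity * number of days that month".

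**The concern.** There are two separate faults.

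**Denominator.** A proportion needs a numerator that is a subset of its denominator. A patient referred from a ward meets this condition. A patient sent home from an emergency department or a clinic need never be admitted to a ward, and on the plain wording is counted only on top. The measure then depends on where referrals come from as well as on how many eligible patients the service takes. If direct referral grows during scale-up, adoption rises for that reason alone.

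**Pathway set.** The text defines one figure over the established pathways together, while Table 3 collects the components pathway by pathway. The article does not say which is analysed. If the pooled figure is used, each new pathway changes its composition. The number of active pathways is also an explanatory factor, so its coefficient would mix a change in uptake with a change in case mix.

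At stake is the interpretation of one primary outcome: its trend, its control-chart signals and its association with the first scale-up priority.

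**Working it through.** The article gives no value for adoption and no ward counts, so there is no stated figure to reproduce. All patient counts below are assumptions chosen to show how the formulas behave.

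**1. Denominator**

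Let N be all patients in a pathway in a month (ward or home), H those admitted to the home service, and D those of H who never passed through a ward.

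- True share: p = H / N
- Ratio as worded: H / (N − D)
- With d = D / H, the ratio as worded equals p / (1 − p·d)

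With N = 200:

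| True share | H | None direct (d = 0) | Half direct (d = 0.5) | All direct (d = 1) |
|---|---|---|---|---|
| 20% | 40 | 40/200 = 20% | 40/180 = 22% | 40/160 = 25% |
| 50% | 100 | 100/200 = 50% | 100/150 = 67% | 100/100 = 100% |
| 60% | 120 | 120/200 = 60% | 120/140 = 86% | 120/80 = 150% |

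The written ratio equals the true share only when every home patient came through a ward. Otherwise it is too high. The excess is small at low uptake and large at high uptake, so it grows as the service succeeds. The ratio passes 1 when H + D exceeds N.

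**2. Pathway set, pooled reading**

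To isolate this effect, the denominator here is all pathway patients.

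- Existing pathways: 40/200 = 20%.
- Add a pathway with 10/200 (5%): (40 + 10)/(200 + 200) = 50/400 = 12.5%. Uptake in the existing pathways is still 20%, and home admissions rise from 40 to 50.
- Same addition while existing pathways improve to 50/200 = 25%: 60/400 = 15%, still below the starting 20%.
- Add instead a pathway with 50/200 (25%): 90/400 = 22.5%, a rise.

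With existing uptake unchanged, the pooled figure falls only when the new pathway's uptake is below the current pooled value. Per pathway, the existing figures do not move in either case.

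**3. Occupancy**

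With an assumed 600 bed days, 25 virtual beds and 30 days:

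- Evaluated left to right as printed: 600/25 × 30 = 720
- With brackets: 600/(25 × 30) = 0.80

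**The case against.** The strongest reply is that the exclusion of direct admissions is a reading of the wording and not a stated rule. The article lists referral sources but does not say how a direct-to-home patient is counted, and calling the measure a proportion suggests that a part of a whole was meant. The data collection forms are in supplementary material that is not shown and may hold a counting rule. This stands, and it limits the claim to the literal wording. It does not remove the point, because the text and Table 3 both name ward admissions as the denominator.

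Table 3 is the best answer on pathway growth. If adoption is analysed per pathway, a new pathway cannot change the existing figures. That is correct, but the text defines the outcome across pathways and nothing says which version is analysed.

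Four stronger inferences are tempting and are not supported:

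- *Ward transfers are double counted.* Appearing in both parts is right for a proportion. With all home patients transferred from wards, the written ratio equals the true share.
- *The ward denominator makes adoption fall.* It biases upward. Only pooled growth can lower the figure.
- *Adoption must fall, or its association must take the wrong sign, as scale-up succeeds.* This needs a pooled analysis and a new pathway of lower uptake. Volume is a separate primary outcome, so growth would still be visible.
- *Occupancy will be reported as 720.* The text calls it a rate and the intent is obvious. The fault is missing brackets, not design.

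It is also fair to say that the study is descriptive, has no comparison group and claims associations only. That lowers the stakes. A descriptive study still depends on its outcome measuring what it names.

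**Conclusion.** The point holds in two parts.

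First, on the literal wording, adoption is not bounded by 1. It overstates uptake whenever some patients are admitted directly home, and it shifts with referral mix. In the illustrations the overstatement runs from 2 to 5 percentage points at a true share of 20% (half or all direct) and from 17 to 50 points at a true share of 50%. The actual size depends on uptake and on the direct-admission fraction, neither of which the article gives.

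Second, the article leaves pooled and per-pathway adoption unreconciled. Under pooling, adding a lower-uptake pathway can lower the figure with nothing changed in the existing pathways (20% to 12.5% in the illustration). The regression on the number of active pathways is then confounded by composition. Under per-pathway analysis this does not arise.

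The occupancy formula is a minor wording correction and carries no weight in this conclusion.

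**What to change.** - **Definition.** For each pathway and month, define adoption as home-service admissions / (home-service admissions + ward admissions never transferred home), for the same pathway and with each patient counted once. With W ward admissions, of which T were transferred home, this is H / (H + W − T).
- **Analysed version.** Reconcile the text with Table 3. Analyse trend and associations per pathway and on the five named pathways as a fixed set over all months. Show later pathways separately from their start month.
- **Occupancy.** Write it as bed days occupied / (virtual bed capacity × days in month).

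Table 3 already lists H and W by pathway. The added item is T, a monthly count of ward-to-home transfers. It should be taken when the counts are extracted from the records: the ethics section says that no individual patient data will be collected, so overlap between monthly totals may not be separable later. The rest is wording.

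### Referrals, acceptance and home visits are ranked as contextual factors although they compose, or follow from, the admissions that the outcomes count

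*Protocol article*

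**What the plan says.** The Measurements and outcomes section sets three primary implementation outcomes:

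- "Volume: number of patient admissions to NUHS@Home and associated bed days per month"
- operational efficiency, the "bed occupancy rate of NUHS@Home, defined as the number of bed days occupied/virtual bed capacity * number of days that month" (read here as bed days divided by the product of capacity and days)
- "Adoption: proportion of patients admitted to NUHS@Home/total patients admitted to affiliated hospital wards for established clinical pathways"

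Table 3 lists the contextual factors, all measured monthly. Under outer context, patient/client characteristics, stand "Number of patients referred for each clinical pathway" and the percentage of "patients accepted and rejected for each clinical pathway". Under inner context, quality and fidelity of monitoring/support, stands "Volume of home visits, during and after office hours". The infrastructure row includes the volume of vendor services.

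The Data analysis section plans unadjusted and adjusted linear regression of each implementation outcome on the continuous factors, with the aim of finding out whether some matter more than others. No row of Table 3 is exempted. The Implementation frameworks section defines contextual influences as lying outside the intervention.

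**The concern.** A ranking of influence is informative only if the candidates could have been unrelated to the outcome. Referrals and acceptance are the two multiplicands of admissions. Home visits are an activity performed on admitted patients; the description of the intervention names them as a key feature of care. Neither home visits nor the service's own decision to accept a patient lies outside the intervention, so Table 3 departs from the protocol's own definition of context.

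Two harms follow. In unadjusted models these measures compete with upstream factors (hospital occupancy, leadership broadcasts, publicity) on unequal terms. In adjusted models they do more damage: a factor that raises admissions by raising referrals loses its apparent effect once referrals, a mediator, or home visits, a consequence, are held fixed. The study asks how to scale up, and a list headed by referrals and home visits says little about that.

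**Working it through.** **1. Identity.** For month *m* and pathway *p*:

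admissions(m) = sum over p of referrals(p,m) × proportion accepted(p,m) × proportion of accepted patients actually admitted(p,m).

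If every accepted patient is admitted, referrals and acceptance fix admissions exactly. On the log scale, with totals over pathways, R-squared is then 1.00.

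**2. Scale.** The Sample size section expects 1,012 admissions in 23 months, and 1,012 / 23 = 44.0 per month. Simulated volume was set near this, at about 40 to 44 per month. The stated pilot rate of 8–10 per month would give 184–230 over 23 months, so the 44 is taken as given. The argument does not depend on it.

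**3. Simulation for admissions.** Inputs, all assumed except the 23 monthly points:

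- mean acceptance 63%, monthly SD 3, 8 or 15 percentage points
- 100%, 90% or 70% of accepted patients admitted
- growth over the period none or about 2.7-fold
- four home visits per admission (0.5, 1 and 2 also tried)
- one genuine upstream driver, acting only through referrals

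Mean R-squared on monthly admissions, as the range over the acceptance SDs and growth patterns, at four visits per admission:

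| Accepted patients admitted | Referrals + acceptance | Home visits alone | Referrals alone | Acceptance alone | Driver alone | Added by driver once the three are in |
|---|---|---|---|---|---|---|
| 100% | 0.97–0.99 | 0.89–0.97 | 0.38–0.93 | 0.10–0.61 | 0.14–0.48 | 0.0003–0.0006 |
| 90% | 0.94–0.98 | 0.88–0.97 | 0.36–0.91 | 0.10–0.60 | 0.14–0.45 | 0.0007–0.0019 |
| 70% | 0.83–0.94 | 0.87–0.96 | 0.35–0.87 | 0.10–0.57 | 0.13–0.40 | 0.0012–0.0039 |

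With fewer visits per admission (8-point SD, growth, 90% admitted), home visits alone explain 0.77 at 0.5 visits, 0.87 at 1 and 0.93 at 2. An unrelated factor scores about 0.04–0.05, as chance predicts with 23 points (1/22 = 0.045). In every simulated study at least one of the three measures outranked the driver. Acceptance alone did so in only 15% to 95%, depending on its SD and the growth trend. Further runs under similar assumptions gave 0.88–0.99 for referrals plus acceptance and 0.83–0.98 for home visits, so the overall ranges are 0.83–0.99 and 0.77–0.98.

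**4. The other outcomes.** Base case: 70 referrals per month before growth, 8-point SD, 90% admitted, 2.7-fold growth, four visits per admission. Further assumptions: about 6 bed days per episode and about 400 ward admissions per month.

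| Outcome | Referrals | Acceptance | Home visits | Driver | One of the three above the driver |
|---|---|---|---|---|---|
| Adoption | 0.80 | 0.17 | 0.93 | 0.16 | 100% |
| Occupancy, capacity fixed | 0.80 | 0.16 | 0.94 | 0.16 | 100% |
| Occupancy, capacity 8 to 20 beds | 0.26 | 0.35 | 0.47 | 0.32 | 83% |

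With capacity fixed, occupancy is bed days divided by a constant, so that row also serves for bed days. When capacity grows with demand the link loosens, and referrals fall below the driver.

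**The case against.** Several objections have weight.

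- **Referral volume is a legitimate measure of demand.** This stands. The fault is ranking it against the factors that generate it, not collecting or reporting it.
- **The near-identity holds for admissions only.** This also stands. Bed days depend on length of stay, adoption on ward admissions, and occupancy on capacity, which is planned to grow (Table 1).
- **Unadjusted models are planned too, the Discussion disclaims causation, and focus groups and triangulation supplement the regressions.** This softens the harm: the driver keeps 0.13–0.48 on its own. But a caveat about association does not cover an association present by definition.
- **A separate analysis plan may choose the covariates.** It may, but this document itself classes the three measures as context and sends every continuous factor into the comparison.

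A reader might infer more than the documents support:

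- **Satisfaction and returns after a change of mind.** "Average patient satisfaction scores" is a mean and the changed-mind item a percentage. Both are measured after admission, but neither rises mechanically with it.
- **Number of active pathways.** It might seem to alter the adoption denominator. Table 3 measures adoption per pathway against ward admissions for the same pathway, so existing ratios need not move. Pathway development is also one of the levers the study sets out to examine.
- **Same-month analysis.** Collection is monthly, but no lag structure is stated. A uniform one-month lag could weaken factors, such as hospital occupancy, that plausibly act within the month.
- **Feedback.** "Interim analyses will be conducted every three months, with feedback provided to the implementation team as needed" suggests that context may partly respond to outcomes. That is a separate matter, partly covered by the meeting records and the annotation of the process control charts.

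**Conclusion.** The point holds for three measures: referrals per pathway, acceptance per pathway and volume of home visits. It extends to vendor service volume where that is a count driven by admitted patients, though this was not simulated. Analysed as written, the plan sets components and consequences of admissions against genuine upstream factors and, in adjusted models, hides factors that work through referrals. For admissions the size is an R-squared of about 0.83–0.99 for referrals plus acceptance, about 0.77–0.98 for home visits, and at most about 0.004 left for the driver.

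These figures rest on assumed acceptance, conversion, growth and visit rates that the documents do not give. The range should be reported rather than one scenario: referrals rising from 20 to 120 a month with acceptance near 60% (SD 6 points) gives 0.98, which lies near the top. The effect is mechanical but looser for bed days and adoption, and weakest for occupancy under growing capacity. Acceptance alone need not rank first. The documents do not support a claim that all listed context is built into the outcomes, or that the study as a whole cannot answer its question. The correction should be made before the association analysis is run.

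**What to change.** 1. In Table 3, move referrals per pathway, percentage accepted and rejected, and volume of home visits into a group of process or intermediate measures. Do the same with vendor service volume where it counts services to admitted patients.
2. In the Data analysis section, state that these measures enter neither the influence ranking nor the adjustment set for volume, adoption and occupancy.
3. Report a monthly funnel of referral, acceptance and admission, and relate the upstream factors to each step.
4. Express home visits per admission or per bed day.
5. Optionally, mark the dates of interim feedback on the process control charts.

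The cost is an edit to one table and one section; Table 3 already lists the measures needed. The downside is that referral volume is shown as a step towards admission instead of being ranked as a demand factor.
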